## Methods and designs

### Study design

The study will be conducted in five hospitals in Beijing, China, including China-Japan Friendship Hospital (Ethical Approval Document No. 2018–82-K57), Beijing Friendship Hospital Affiliated with Capital Medical University (2019-P2–016-02), Beijing Hospital of TCM Affiliated with Capital Medical University (2018BL-057-02), Wangjing Hospital of China Academy of Traditional Chinese Medicine (WJEC-KT-2018-045-P001), and Beijing Chaoyang Hospital Affiliated with Capital Medical University (2018-KE-313).

The study design flow chart is shown in Fig. 1. The trial will use stratified random grouping. Eligible subjects will first undergo UGT1A1 gene testing and be stratified to one of two levels, low or moderate-to-high risk of CRD, after which they will be randomly allocated to the SXD treatment cohort or the placebo cohort within their risk group. Patients will be excluded if UGT1A1 testing fails for any reason. The trial will include two cycles of chemotherapy (21 days per cycle), and each cycle will consist of 14 days of oral administration of SXD or placebo beginning 3 days before initiation of chemotherapy, with a follow-up visit from the initiation of chemotherapy. The trial schedule, including patient enrollment, interventions, and outcome measurements is shown in Fig. 2.

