### Subject withdrawal criteria

Study participation will be terminated if:
A severe adverse event (AE) occurs during chemotherapy;The chemotherapy schedule requires modification because of severe adverse reactions to chemotherapy;Subjects do not comply with this study’s requirements.

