### Intervention

All subjects will receive two cycles of irinotecan-based chemotherapy according to the 2018 National Comprehensive Cancer Network (NCCN) Clinical Practice Guideline for SCLC (version 2.0) as follows: intravenous infusion of irinotecan 65 mg/m^2^ body surface area (BSA) and cisplatin 30 mg/m^2^ on days 1 and 8, administered 3 weeks apart.

SXD and placebo will be manufactured by the pharmaceutical company New Green Science and Technology Development Co. Ltd., of Sichuan, China, according to Good Manufacturing Practices (GMP) for Pharmaceutical Products, People’s Republic of China. SXD comprises eight Chinese herbs (as shown in Table 1) that will be extracted and concentrated using a standardized Chinese formula. The resulting granules will be packed in aluminum foil bags as is permitted and regulated by the China Food and Drug Administration (CFDA). The placebo will consist of maltodextrin, starch, bitters, and food coloring, and will have a similar appearance, color, weight, taste, smell, and packaging to SXD. The participants will be instructed to dissolve their SXD or placebo and take it as a dose of 3.2 g (per bag) each time, twice daily, beginning 3 days before each cycle of chemotherapy to 11 days after the start of chemotherapy. Participants will be given antidiarrheal medication if they develop diarrhea, according to the CRD specialist consensus and guidelines [5], as detailed in Fig. 3.

**Table 1 Tab1:** Constituents of Shengjiang Xiexin decoction (SXD)

Chinese name	Botanical latin name	Proportion
Shengjiang	*Rhizoma zingiberis recens*	4
Ganjiang	*Rhizoma zingiberis*	1
Huangqin	*Radix scutellariae*	3
Huanglian	*Rhizoma coptidis*	1
Banxia	*Rhizoma pinelliae*	3
Dangshen	*Radix codonopsis*	3
Dazao	*Fructus jujubae*	4
Gancao	*Radix glycyrrhizae*	3

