### Statistical analysis

The study data will be managed and analyzed by an independent biostatistician using SPSS (Statistic Package for Social Science, v20.0). This study includes four data sets for analysis: intention to treat (ITT), per-protocol set (PPS), full analysis set (FAS), and safety set (SS).

ITT analysis will be used to analyze the primary outcome for SXD efficacy in preventing or reducing the incidence and severity of CRD, and will include all study participants. Any missing primary outcome data will be supplemented by carrying forward the last recorded data.

PPS analysis will be performed to test the robustness of the ITT analysis and will only include participants who strictly follow the protocol and finish the study. The results from the two analyses will be considered credible if they are consistent; otherwise, the results will require sufficient discussion and explanation. Furthermore, is compliance is too low, CACE analysis will be implemented to provide an unbiased and robust estimation of treatment effect. The analysis of secondary outcomes will be based on the results of the PPS analysis.

The FAS analysis will include all randomized participants who completed at least one treatment and one follow up. To analyze the intervention-related AEs, the SS analysis will evaluate all safety outcomes for every randomized participant who received any intervention at least once during the study period.

Continuous data will be presented as the mean and standard deviation (SD), and noncontinuous data (including categorical or ranked data) will be presented as count and number (percentage). We will analyze categorical data as the risk ratio (RR) with 95% confidence intervals (CI), and analyze continuous data as mean differences (MD) and their 95% CI.

The incidence of diarrhea, modification rate of the chemotherapy regimen, and incidence of hospitalization are categorical data. The chi-square test or Fisher’s exact test will be conducted to compare the differences in those data between two groups. The Wilcoxon rank sum test will be conducted to evaluate the difference in ranked data between the two groups, which includes the grade of diarrhea and evaluation of chemotherapy efficacy. Repeated-measures analysis of variance (ANOVA) will be used to compare continuous values such as the use of antidiarrheal drugs. In all tests, a *P* value of < 0.05 will be considered statistically significant.

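### The added CACE analysis is called unbiased, but non-compliers' outcomes are cut short and partial intake is possible, so it can be biased in either direction

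*Protocol article*

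**What the plan says.** All references are to the protocol article.

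- **Statistical analysis.** ITT is the analysis of the primary outcome and the per-protocol set tests its robustness. As a further step, if compliance is too low, "CACE analysis will be implemented to provide an unbiased and robust estimation of treatment effect". For the primary outcome, "Any missing primary outcome data will be supplemented by carrying forward the last recorded data".
- **Subject withdrawal criteria.** Study participation is terminated in three situations. One is "Subjects do not comply with this study’s requirements". Another is "The chemotherapy schedule requires modification because of severe adverse reactions to chemotherapy".
- **Study design and Intervention.** Under the first, "each cycle will consist of 14 days of oral administration of SXD or placebo". Under the second, the product is taken "twice daily, beginning 3 days before each cycle of chemotherapy to 11 days after the start of chemotherapy".
- **Primary outcome.** CRD counts from more than 24 hours after irinotecan until both chemotherapy cycles are complete. It is therefore a cumulative event over the whole two-cycle window.

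**The concern.** The complier average causal effect (CACE) in its usual form is the ITT difference divided by the proportion of compliers in the active arm. Calling it unbiased requires, among other things, that:

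1. the outcomes of non-compliers are known in both arms over the full endpoint window, because they enter the ITT numerator; and
2. assignment to SXD has no effect on the outcome of those classed as non-compliers (the exclusion restriction).

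The article works against both. Ending participation for non-compliance, and not only the study product, means a non-complier who has had no CRD by then is carried forward as event-free, although part of the risk window remains. And with 28 dosing days at two doses a day (about 56 doses), a participant can take a substantial part of the course and still be counted as a non-complier.

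CACE would be invoked exactly when compliance is poor, which is when these distortions are largest. Readers would then be told that this estimate is the unbiased one. Outcomes never collected cannot be recovered by a later definition in an analysis plan.

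**Working it through.** **Inputs from the article (Sample size):** CRD risk 63.4% without SXD and 37.5% with SXD. Taken as the true effect in compliers, this is 63.4 − 37.5 = 25.9 points. The article gives no compliance rate and no CACE figure, so there is no stated result to reproduce.

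**Assumptions (mine):** the non-compliance rates; constant hazard; non-compliers leave half-way through follow-up; the fraction of benefit kept by partial takers. Compliers and non-compliers have the same underlying risk.

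**Formula:** CACE = (recorded placebo risk − recorded SXD risk) / compliance in the SXD arm.

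**A. Truncation with carry-forward; non-compliers get no effect.** Untreated risk recorded by half-time is 1 − √(1 − 0.634) = 0.395.

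| Non-compliance SXD / placebo | Recorded SXD risk | Recorded placebo risk | ITT | CACE |
|---|---|---|---|---|
| 30% / 10% | 0.7×0.375 + 0.3×0.395 = 0.381 | 0.9×0.634 + 0.1×0.395 = 0.610 | 0.229 | 0.229/0.7 = 32.7 points |
| 10% / 30% | 0.9×0.375 + 0.1×0.395 = 0.377 | 0.7×0.634 + 0.3×0.395 = 0.562 | 0.185 | 0.185/0.9 = 20.6 points |
| 30% / 30% | 0.381 | 0.562 | 0.181 | 0.181/0.7 = 25.9 points |

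Against 25.9, these are about 26% too large, about 20% too small, and unbiased.

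The same error is already in ITT. With complete outcomes, ITT in the first row would be 0.7×0.259 = 0.181, but 0.229 is recorded (26% too large). In the second row it would be 0.9×0.259 = 0.233, but 0.185 is recorded (about 20% too small). With no true effect and a 30% / 10% split, the recorded risks are 0.562 (SXD) and 0.610 (placebo). That is a false ITT difference of 4.8 points, which CACE rescales to 0.0478/0.7 = 6.8 points.

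**B. Complete outcomes, but partial takers are classed as non-compliers and keep half the effect (0.1295).**

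- 20% stop: (0.8×0.259 + 0.2×0.1295)/0.8 = 29.1 points (1.13 times the truth).
- 30% stop: (0.7×0.259 + 0.3×0.1295)/0.7 = 31.5 points (1.21 times).
- If they keep none of the effect, the ratio is 1.00 at every compliance level.

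**C. Both together: 40% in each arm take cycle 1, then stop.** Cycle 1 risk is 1 − √(1 − 0.375) = 0.209 on SXD and 0.395 on placebo.

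- Terminated and carried forward: SXD 0.6×0.375 + 0.4×0.209 = 0.309; placebo 0.6×0.634 + 0.4×0.395 = 0.538; CACE = 0.2296/0.6 = 38.3 points.
- Followed to the end of cycle 2: the risk in SXD stoppers is 1 − √(0.625×0.366) = 0.522; SXD 0.6×0.375 + 0.4×0.522 = 0.434; placebo 0.634; CACE = 0.2003/0.6 = 33.4 points.

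Equal stopping therefore removes the bias only if the doses already taken did nothing. Continued follow-up removes the truncation part; what remains depends on who is called a complier.

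**The case against.** Much of the case on the other side stands.

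- **CACE does not replace ITT.** A reader might infer that the plan switches to CACE when compliance is poor. The text adds it as a further step, and ITT remains the primary analysis.
- **Inflation is not established.** A reader might infer that CACE always exaggerates SXD's effect. Reversing the assumed split turns a 26% overstatement into an understatement of about 20%. The trial is blinded with a matched placebo, and nothing in the article says which arm would comply less. In case A, direction is an input, not a result.
- **Truncation is not a CACE fault.** It comes from termination with carry-forward and reaches ITT first. This is correct, and it shapes the fix.
- **Case B needs a complier definition that the article does not give.** If any intake counts as compliance, CACE is close to ITT and the inflation disappears. Partial intake is a foreseeable deviation, not planned dosing.
- **The missing value for too-low compliance and the missing complier definition** are details that an article may leave to the full protocol or SAP, neither of which is shown. A reader might infer a decision taken after the data are seen; the document does not show that.
- **Stopping because of CRD** does little harm here, since the event is already recorded and carry-forward keeps it.

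None of this rescues the claim that the estimate is unbiased. Bias in either direction contradicts it, and the termination rule and the carry-forward rule are both stated in the article.

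**Conclusion.** The property claimed for CACE is not supported by the design as written. Non-compliers' CRD outcomes are not secured to the end of cycle 2, and partial intake makes the no-effect assumption for non-compliers doubtful. On the assumed values, a true 25.9 points is estimated as anything from 20.6 to 32.7 points through truncation alone, depending on which arm complies less, and as 29.1 to 31.5 points through partial intake alone at 20% to 30% stopping. Balanced stopping with no effect in non-compliers gives no bias. The partial-intake component, where it applies and SXD works, pushes upward; the truncation component can go either way. All sizes rest on assumed compliance, because the article reports none.

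CACE is a conditional, supportive analysis, so its label alone is a modest problem. The underlying loss of outcomes matters more, because it also affects the primary ITT comparison.

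**What to change.** 1. Continue diary collection of CRD to the end of cycle 2 for every randomized participant, including those who stop product or do not comply. Separate the end of study treatment from the end of outcome collection in the withdrawal section. This concerns data collection only and leaves decisions about treatment untouched.
2. Use these observed outcomes in place of carry-forward in both ITT and CACE.
3. Delete the description of CACE as unbiased and robust.
4. Keep ITT as the efficacy conclusion. Label CACE supplementary, state its assumptions, and fix the complier definition before unblinding.

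Dropping CACE without steps 1 and 2 would leave the truncation bias in ITT. Steps 1 and 2 without step 4 would leave the partial-intake problem (33.4 points in case C).

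**Cost:** slightly more follow-up data collection with a diary already in use, some wording changes, and a possibly less favourable supportive estimate. Step 1 has to be in place while participants are still under follow-up.

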#### Secondary outcomes

Secondary outcomes include the degree of diarrhea, degree of neutropenia, incidence of chemotherapy regimen alterations, amount and dose of antidiarrheal drugs taken, incidence of hospitalization for diarrhea, and evaluation of chemotherapy efficacy.

Each participant will be supplied with a diary in which they will be instructed to record the time, duration, and coexisting symptoms of diarrhea. The information will then be reported to the researchers. The grade of diarrhea will be assessed for each chemotherapy cycle, and the most serious grade for each participant will be recorded to compare the difference in grades between the SXD and placebo cohorts. The diarrhea grading criteria used will be in compliance with the Common Terminology Criteria for Adverse Events (CTCAE), Version 5.0, released by the National Cancer Institute (NCI), which is detailed in Table 2. In addition, to completely evaluate each episode of diarrhea, participants will be instructed to record in detail the duration of diarrhea and the presence of coexisting symptoms, such as stomachache, abdominal distension, and cramps.

**Table 2 Tab2:** Diarrhea grading criteria

Grade of diarrhea	Definition
**Grade 1**	Increase of < 4 stools per day from baseline; mild increase in ostomy output compared to baseline
**Grade 2**	Increase of 4–6 stools per day from baseline; moderate increase in ostomy output compared to baseline; limiting instrumental ADL
**Grade 3**	Increase of ≥ 7 stools per day from baseline; hospitalization indicated; severe increase in ostomy output compared to baseline; limited self-care in ADL
**Grade 4**	Life-threatening consequences; urgent intervention indicated
**Grade 5**	Death

*ADL* activities of daily living

The development of diarrhea can affect the chemotherapy dose, duration, and schedule. Therefore, alterations in the chemotherapy schedule will be calculated in each group, including dose reductions, treatment postponement or termination, and other alterations in the preplanned chemotherapy regimen. If serious diarrhea occurs, antidiarrheal drugs and even hospitalization may be required, as determined by the recommended guidelines and expert consensus. The amounts and doses of antidiarrheal drugs prescribed and the incidence of hospitalization will be recorded. Common antidiarrheal drugs are loperamide and berberine hydrochloride [21, 22].

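### Secondary outcomes are assigned to the per-protocol set, but the withdrawal criteria remove patients with severe events from that set, so severe-event outcomes are truncated and tumour response is compared among completers only

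*Protocol article*

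**What the plan says.** Four parts of the protocol article bear on this.

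- **Statistical analysis, set for secondary outcomes:** "The analysis of secondary outcomes will be based on the results of the PPS analysis". The PPS "will only include participants who strictly follow the protocol and finish the study".
- **Subject withdrawal criteria:** participation is terminated if "A severe adverse event (AE) occurs during chemotherapy", or if "The chemotherapy schedule requires modification because of severe adverse reactions to chemotherapy". Non-compliance is the third reason.
- **Secondary outcomes:** besides the degree of diarrhea and of neutropenia, the list is "incidence of chemotherapy regimen alterations, amount and dose of antidiarrheal drugs taken, incidence of hospitalization for diarrhea, and evaluation of chemotherapy efficacy". Regimen alterations are described as "including dose reductions, treatment postponement or termination, and other alterations in the preplanned chemotherapy regimen". In Table 2, the grade 3 definition contains "hospitalization indicated; severe increase in ostomy output compared to baseline".
- **Statistical analysis, intention-to-treat (ITT) set:** ITT is used for the primary outcome, described as "SXD efficacy in preventing or reducing the incidence and severity of CRD". The Primary outcome section names only the incidence and percentage of chemotherapy-related diarrhea (CRD).

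The safety set covers safety outcomes in every treated participant. The full analysis set is defined, but no outcome is assigned to it.

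**The concern.** An analysis set should not depend on the outcome it is used to measure. Here, a patient whose chemotherapy is changed because of a severe reaction has had a secondary outcome event. The same event ends participation, so the patient does not complete the study and is outside the PPS. The same chain applies to severe diarrhea and, through it, to hospitalization for diarrhea.

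If SXD works, more of these patients are lost from placebo than from SXD. The comparison is then no longer between the groups that were randomized, and the events that would show the benefit are the ones removed. Tumour response is also at stake, because it is meant to show whether SXD interferes with chemotherapy. It is assessed after two cycles, so patients withdrawn earlier are not compared at all.

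**Working it through.** The plan gives no figure of its own on this point, so there is none to reproduce. The check has two parts: reading the sections together, and sizing the effect.

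**1. Which outcomes are affected**

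| Secondary outcome | Effect of the withdrawal criteria combined with the PPS |
|---|---|
| Regimen alteration due to severe reactions | Excluded by the rule itself |
| Regimen alteration for other reasons | Can remain |
| Grade 3–4 diarrhea | Excluded if a severe adverse event means grade 3–4, the sense in which Background uses severe for diarrhea |
| Hospitalization for diarrhea | Mostly excluded, since Table 2 ties it to grade 3 |
| Grade 1–2 diarrhea, antidiarrheal use for it | Remains |
| Neutropenia | Severe cases excluded from the PPS; hematologic toxicity is also covered by the safety set |
| Tumour response | Completers of two cycles only |

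**2. Size of the effect**

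Inputs:
- 50 per arm (Sample size).
- Severe event rate on placebo *p* = 11% to 32% (Background, range for severe irinotecan diarrhea).
- Severe event rate on SXD: half the placebo rate, 5.5% to 16%. This is an assumption.
- *f* = share of patients with a severe event who are withdrawn and so leave the PPS. Values 0.5, 0.8 and 1 are assumptions; *f* = 1 is the rule as written.

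Formulas, per arm:
- events left = 50 × *p* × (1 − *f*)
- patients left = 50 × (1 − *pf*)
- PPS rate = *p*(1 − *f*) / (1 − *pf*)

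Worked case, 32% versus 16% with *f* = 0.5:
- placebo: 0.16 / 0.84 = 19.05%
- SXD: 0.08 / 0.92 = 8.70%
- difference: 10.4 points, against 16 points in all randomized patients

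| Rates, placebo vs SXD | *f* | Events left | Patients left | Difference (points) |
|---|---|---|---|---|
| 32% vs 16% | 0 (all randomized) | 16 vs 8 | 50 vs 50 | 16.0 |
| | 0.5 | 8 vs 4 | 42 vs 46 | 10.4 |
| | 0.8 | 3.2 vs 1.6 | 37.2 vs 43.6 | 4.9 |
| | 1 | 0 vs 0 | 34 vs 42 | 0 |
| 11% vs 5.5% | 0 (all randomized) | 5.5 vs 2.75 | 50 vs 50 | 5.5 |
| | 0.5 | 2.75 vs 1.4 | 47.2 vs 48.6 | 3.0 |
| | 0.8 | 1.1 vs 0.55 | 45.6 vs 47.8 | 1.3 |
| | 1 | 0 vs 0 | 44.5 vs 47.2 | 0 |

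In every row with *f* above 0, the difference shrinks and the two arms lose different numbers of patients.

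**3. Severity**

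The ITT sentence includes severity with the primary outcome. The Secondary outcomes section lists degree of diarrhea as secondary, and the PPS sentence covers secondary outcomes without exception. Diarrhea grade is therefore assigned to two different sets.

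**The case against.** The strongest reply is that the damage is limited, and much of that reply stands.

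- **The primary outcome is protected.** CRD incidence is analysed by ITT, with the PPS as a robustness check and any disagreement to be discussed. A reader might infer that selection into the PPS also spoils the incidence result. The documents do not support that, because the quoted sentence governs secondary outcomes only.
- **Not every secondary outcome is emptied.** A reader might infer that all are empty by construction. The criteria act on severe events and non-compliance, so milder diarrhea, milder neutropenia, antidiarrheal use for milder diarrhea and non-severe alterations stay in.
- **Zero events is the limiting case.** The withdrawal criteria do not grade a severe adverse event. The safety outcomes text and Quality control speak of modifying chemotherapy without mentioning withdrawal, so the rule may be applied only in part. This is why the table includes *f* below 1.
- **Early progression is not a listed withdrawal reason.** A reader might suppose that progressing patients are removed from the response comparison. Only loss through severe toxicity or non-compliance is documented, and the direction of any resulting bias cannot be stated.
- **Diarrhea grade might be rescued by the ITT sentence, and neutropenia by the safety set.** Partly so. For grade, however, the text contradicts itself, and no set other than the PPS is given for regimen alteration, hospitalization or response.

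A separate analysis plan does not answer the point. The article does not leave the set open; it names one, and an analysis plan that follows it would carry the problem forward.

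**Conclusion.** The concern holds for outcomes driven by severe events, for tumour response as a comparison of completers, and for the contradiction on severity. Applied as written, the two rules remove alterations caused by severe reactions in both arms, and most grade 3–4 diarrhea and related hospitalization, whatever SXD does. In the illustration, the 16 to 8 contrast disappears under full application, and the difference falls from 16 to 10.4 points if half are withdrawn.

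The sizes rest on a background incidence range, an assumed halving on SXD, assumed withdrawal shares, and reading a severe adverse event as grade 3–4. The structural fault needs only the last of these for diarrhea grade and hospitalization, and none of them for regimen alterations due to severe reactions. The primary incidence analysis is not affected by this sentence.

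**What to change.** 1. Replace the sentence on secondary outcomes so that they are analysed in all randomized participants as randomized, with the PPS as supportive only.
2. State that the event that triggers withdrawal counts as an outcome, and that outcome data continue to be collected after study treatment stops, to the end of the second cycle and the response assessment. Without this, the all-randomized label does not supply the missing data.
3. Assign diarrhea severity to the all-randomized analysis as a secondary outcome, and remove it from the description of the primary analysis.
4. For tumour response, report how many patients per arm are not evaluable, and add a sensitivity analysis counting them as non-responders. The planned rank test can stay as the main analysis.
5. Reconcile Subject withdrawal criteria, Secondary outcomes and Statistical analysis. No view is taken here on the clinical withdrawal rule itself.

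The cost is small: a few sentences of text, some follow-up of withdrawn patients, and some response data that will still be missing. No additional patients are needed.
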